#### Prior experience and skills in BBN

To control for possible differences in prior experience and skills in BBN, we developed a 3-item questionnaire (see supplementary material). Participants will have to state on 2 “yes/no” items if they have prior practical experience in or theoretical knowledge of BBN principles (if so, participants will need to specify in a free text field to what extend). On an additional item, participants will rate their perceived skill level in BBN from 1 “very low” to 7 “very high”.

#### BBN interest and motivation

Participants will report to what degree they are interested in BBN and motivated to do well at the BBN task using two 7-point scales (1 “very little interest” to 7 “very interested”; 1 “not at all motivated to perform well” to 7 “absolutely motivated to perform well”). Interest and motivation will be used as control variables.

### Interventions

The interventions will be part of the learning phase and complement a written version of the SPIKES protocol, which all participants receive, regardless of their condition (see Fig. 3).

### Stress arousal reappraisal

The content of the stress arousal reappraisal intervention is adapted from previous research [47, 61, 62, 69, 87, 99] and presented in the form of a 7-minute screencast using illustrations and voice-over. The screencast states that experiencing stress arousal is normal and legitimate and shows that an individual cares about a challenging situation. More specifically, participants will learn how stress arousal fulfills a vital function (e.g., an increased heart rate provides more oxygen to where it is needed) and is necessary for individuals to perform at their best. Therefore, stress arousal should be perceived as functional and beneficial for performance rather than harmful. To endorse the presented information, participants will then be asked to reflect on past and future stressful situations. Finally, right before the BBN communication task, participants will be reminded to reappraise the stress arousal they might experience in the encounter as beneficial for their BBN performance.

In the corresponding control condition, participants will be shown a 7-minute screencast about psychological and neurological learning processes (this is similar to control materials successfully used in previous studies, e.g., [87]).

### Worked example

The WE will be presented in the form of a 10-minute video showing a simulated BBN encounter between a physician and a patient. The BBN encounter will be structured according to the six-step SPIKES protocol, with the physician performing each step appropriately. For instance, in the step *Knowledge*, the physician first announces that they have bad news, before delivering the specific diagnosis (“Unfortunately, I do not have any good news for you today”). Each of the steps is accompanied by a written hint, emphasizing which step is being displayed and why it is done in this way (in accordance with Lorch [100]). During the same period of 10 min, participants attributed to the corresponding control condition will continue working with the written SPIKES protocol.

**Fig. 3 Fig3:**
[figure not shown]
Illustration of the learning module *Note*: A general “Introduction of the BBN module” and “The six-step SPIKES framework” will be provided to participants of all groups. The worked example (“Demonstration”) and stress arousal reappraisal (“Optimizing stress arousal”) interventions will only be presented in the respective groups

### Statistical analysis plan

To test the effectiveness of the interventions on communication performance (H1.2, H2.2), we will use 2 (SAR vs. no SAR) x 2 (WE vs. no WE) between-subjects ANOVAs. For the analysis of the repeated psychophysiological stress response outcomes (H1.1, H2.1), we will use linear mixed models with the participants as random effect. To test if the effects of the interventions on communication performance are mediated by the psychophysiological stress response (H3.1, H3.2), we will conduct a bootstrapping mediation analysis following state-of-the-art methodology [101]. We will follow international guidelines to derive the parameters used in the statistical analysis. For each cardiovascular measure, the mean of each 1-minute period will be calculated. For salivary measures, the area under the curve with respect to ground and increase will be computed. Where sensible, we will transform skewed variables to approach normality. We will perform sensitivity analyses with the control variables gender, age, BMI, use of hormonal contraceptives, shift work, SP, stress mindset, depression anxiety and stress, body motion, BBN-related interest & motivation, BBN-related prior experience & skills, and habitual use of emotion regulation strategies. For significance testing, an alpha level of 0.05 will be used.

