
**Fig. 2 Fig2:**
[figure not shown]
Experimental Session *Note*: Q1 contains the Multidimensional Mood State Questionnaire (MDMQ) and Stress Mindset Measure (SMM). Q2 contains the MDMQ, self-reported demands and resources, prior BBN experience and skills, and BBN interest and motivation. Q3 and Q4 both contain the MDMQ and self-reported demands and resources. Q5 includes the Depression, Anxiety and Stress Scale (DASS-21), Emotion Regulation Questionnaire (ERQ), SMM and MDMQ. Q6 contains the MDMQ

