### Experimental session measures

From the measures obtained during the experimental session, we will derive primary outcomes, which will be used for hypothesis testing, and secondary outcomes, which will be used as control variables in the primary analyses or for exploratory analyses.

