#### BBN-skills performance

Participants’ skills performances as shown during the BBN encounter will be scored by three independent raters based on video recordings. Raters will be trained on an adapted version of the SPIKES scale (see supplementary material) [90] and the ‘global Breaking Bad News Assessment Scale’ (glBAS) [91]. The adapted SPIKES scale contains one item for the steps Setting, Knowledge, Emotions, Strategy & Summary and two items for Perception and Invitation (for these two steps, the mean of the two items will be used). An additional item assesses non-verbal communication aspects. All items are rated on a bipolar five-point rating scale ranging from 1 to 5 (the higher the better). The glBAS contains 5 items [91]. Each item represents different domains of BBN and is rated on a 5-point Likert scale ranging from 1 “very good” to 5 “very poor”. We will reverse the values of the original glBAS items to match the SPIKES scale. For the SPIKES scale, the final score is the grand mean of all steps and the non-verbal communication item across the three raters. Each step as well as the non-verbal item will be weighted equally. For the glBAS, the final score will be the grand mean across the 5 items and three raters. Communication performance is a primary outcome used for hypothesis testing.

The raters’ training will be structured according to previous research [90] and given by [name]. During approximately three days of training, raters will be presented with an introduction to BBN and critical literature, and the assessment methods will be discussed. Raters will then independently score video examples covering low, mediocre, and high student BBN-related performances by using the two scales. Each evaluation run will be followed by a group discussion during which raters are requested to reach a consensus on evaluation results.

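### The article leaves unsettled whether the model deciding H1.2 and H2.2 is covariate-adjusted, and the unadjusted ANOVA it names may forgo precision that pre-intervention data would give at almost no cost

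*Protocol article*

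**What the plan says.** The BBN-skills performance section gives the outcome its status: "Communication performance is a primary outcome used for hypothesis testing". It is scored once, from the video of the simulated encounter, so it has no baseline value of its own.

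For H1.2 and H2.2 the Statistical analysis plan section states "we will use 2 (SAR vs. no SAR) x 2 (WE vs. no WE) between-subjects ANOVAs". No covariate is named.

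The note to Fig. 2 places the relevant background measures in the second questionnaire, before the learning phase that contains the interventions: "Q2 contains the MDMQ, self-reported demands and resources, prior BBN experience and skills, and BBN interest and motivation". Their purpose is stated in the Measures sections: "To control for possible differences in prior experience and skills in BBN, we developed a 3-item questionnaire", and "Interest and motivation will be used as control variables".

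Two statements then say where control variables are used. The Statistical analysis plan section has "We will perform sensitivity analyses with the control variables gender, age, BMI", in a list that ends with "BBN-related interest & motivation, BBN-related prior experience & skills, and habitual use of emotion regulation strategies". The Experimental session measures section describes "secondary outcomes, which will be used as control variables in the primary analyses or for exploratory analyses". The end of the Hypotheses section and the Possible pitfalls section both assign stress mindset, as a control variable, to the primary analysis.

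**The concern.** There are two linked difficulties. First, the sections do not agree on whether the analysis that decides H1.2 and H2.2 carries covariates. If this is not fixed before the data are seen, either an adjusted or an unadjusted result could be presented as the main one.

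Second, if the unadjusted ANOVA is the deciding model, any performance variance that the pre-intervention measures explain stays in the error term. The design has almost no spare power, so even a small gain is worth having when the data are collected anyway. The listed sensitivity analyses do not clearly supply a baseline-adjusted estimate, because the list mixes pre-intervention variables with some measured during or after the intervention period.

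**Working it through.** **Inputs.** From Sample size calculation: d = 0.40, two-sided alpha 0.05, target power 0.80, 50 per group, N = 200. A main effect in the 2 x 2 design compares 100 with 100. From Study design: randomisation stratified by gender. The share of performance variance explained by the covariates (R²) is not in the document and is assumed.

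**Reproducing the plan's figure.** The normal approximation per factor level is 2 × (1.960 + 0.842)² / 0.40² = 98.1, rounded up to 99, so 198 in total. For the exact test, the noncentrality is d × √N / 2 = 0.40 × √200 / 2 = 2.828. With 200 − 4 = 196 error degrees of freedom, power is 0.8036. At N = 198 it is 0.7996. The smallest N that reaches 0.80 is 199, or 200 if the four cells are equal. The stated N = 200 is therefore the size for the unadjusted main effect.

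**Adding covariates.** Take five: gender, self-rated skill, theoretical knowledge, interest and motivation. The residual SD is multiplied by √(1 − R²), so the noncentrality becomes 2.828 / √(1 − R²). The error degrees of freedom fall to 196 − 5 = 191.

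| Model | R² (assumed) | Noncentrality | Power at N = 200 | N for 0.80 power |
|---|---|---|---|---|
| Unadjusted | – | 2.828 | 0.8036 | 199 |
| Adjusted | 0 | 2.828 | 0.8035 | – |
| Adjusted | 0.02 | 2.857 | 0.8113 | 195 |
| Adjusted | 0.05 | 2.902 | 0.8231 | 189 |
| Adjusted | 0.10 | 2.981 | 0.8429 | 179 |

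If the covariates predict nothing, the cost is 0.0001 in power. If they explain 2% to 10%, the gain is about 1 to 4 percentage points.

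**Which model decides.** Setting the sections side by side:

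- Statistical analysis plan: ANOVA without named covariates, with control variables in sensitivity analyses.
- Experimental session measures: measures used as control variables in the primary analyses.
- Hypotheses and Possible pitfalls: stress mindset as a control in the primary analysis.

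The last three cannot be squared with the first if all refer to the model that tests the hypotheses.

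**Timing of the listed control variables.** Skill, knowledge, interest and motivation come from the second questionnaire, before the learning phase. DASS-21 and the emotion regulation questionnaire come from the fifth, after the encounter. Stress mindset is measured at the first and fifth questionnaires, and the list does not say which value is meant; the article also treats it as something SAR may change. Body motion is recorded by the VU-AMS during the session. Only variables fixed before the intervention can be entered without risk to the randomised comparison.

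**The case against.** The strongest reply is that nothing is wrong with the test. An unadjusted 2 x 2 ANOVA is valid in a randomised factorial trial, and N = 200 was computed for it. That stands in full: this is an efficiency gain not taken, together with an inconsistency in the text.

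A reader might infer that the plan ignores these measures. It does not, because both sets are named in the sensitivity list. Nor does the text say that every listed variable enters one model together; it speaks of sensitivity analyses in the plural.

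A reader might also infer that chance imbalance in skill or motivation distorts the SAR and WE estimates. The documents do not support this. Imbalance arising by chance after randomisation is not bias, and its contribution is already in the unadjusted standard error, which is 2 / √200 = 0.14 SD, with a 95% half-width of 1.96 × 0.14 = 0.28 SD (rounded).

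The gain may well be small. Eligibility requires no prior BBN experience, so the practical-experience item should hardly vary. Knowledge is a yes/no item and skill a single self-rating by novices. All participants study the SPIKES protocol between these ratings and the encounter. This stands, and it is why larger values of R² are not pressed here.

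It can also be said that the Experimental session measures sentence is general and joins its two uses with an either/or, so it need not mean that every control variable enters every primary test, and that an article condenses a fuller plan. But the two statements on stress mindset are specific to the primary analysis, and the Statistical analysis plan section states a deciding model outright. The conflict lies within what is printed.

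**Conclusion.** The point holds in a limited form. The article does not settle whether the model deciding H1.2 and H2.2 is adjusted, and if it is the unadjusted ANOVA, some precision on a primary outcome may be lost that could be had at practically no cost. The size is modest: power of about 0.81, 0.82 or 0.84 instead of 0.804, for an assumed R² of 0.02, 0.05 or 0.10. These figures rest on d = 0.40, 200 valid cases, five covariates and an R² that the documents do not give. They do not show that the trial is underpowered or that its planned test is biased. The improvement is worth making because the downside is negligible even if the covariates explain nothing.

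**What to change.** Name one deciding model for H1.2 and H2.2 before any data are seen: a 2 x 2 ANCOVA with gender, as the stratification factor, and a short fixed list from the second questionnaire, namely self-rated BBN skill, theoretical BBN knowledge, interest and motivation. Admit no variable measured after the intervention to that model. Keep the unadjusted ANOVA as the sensitivity analysis.

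Align the four places that describe control variables (Hypotheses, Experimental session measures, Statistical analysis plan, Possible pitfalls) so that each says the same about which variables enter the primary and which the sensitivity analyses. If stress mindset stays in any adjusted model for these hypotheses, state that the value from the first questionnaire is used.

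The cost is a few sentences and five of 196 error degrees of freedom. No new data or participants are needed.

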### Sample size calculation

An a-priori power analysis was performed to calculate the required sample size, using the G*Power 3 program [102]. We reviewed published data on psychophysiological and performance effects of our two interventions, to determine that an effect size of *d* = 0.40 [103] is scientifically reasonable and practically relevant. Given an alpha level of 0.05 (two-tailed) and a targeted power level of 0.80, *n* = 50 participants per group will be required. Thus, we will need a total of *N* = 200 participants with valid data to test our hypotheses. In case of device malfunctioning, dropouts, non-compliance or unusable data, additional participants will be scheduled until a total of 200 valid cases is reached.

## Discussion

### Implications

We anticipate the findings of the current project to have several important implications for theory and practice. Findings will provide unique insights into the psychophysiology of medical students who are tasked with BBN. Psychophysiological stress responses elicited in BBN encounters might be meaningfully mapped on to and understood from the challenge and threat perspective. In a next step, differences in stress responses can be linked to the level of communication performance. Most importantly, we propose two short interventions—stress arousal reappraisal and worked examples—that might not only improve students stress responses, but also cause cascading effects on communication performance.

If proven effective, findings may open new avenues for innovations in medical education. Not only do we provide a novel and more comprehensive understanding of BBN encounters, but we also propose low threshold interventions that could be easily incorporated into the curriculum of medical students. Further, we expect the benefits of stress arousal reappraisal to spill over to similar stress-inducing communications with patients or other motivated performance situations, which are ubiquitous in education and the medical workplace environment (e.g., [48, 68, 104]). Finally, improved communication also benefits health related outcomes of concerned patients [14–20].

The current project might further contribute to the advancement of the BPSM of challenge and threat. For the first time, we will assess the well-established psychophysiological indices of challenge and threat (self-reported demands and resources, cardiovascular parameters), together with less often used indices of the activity of the HPA and SAM axes (sC, sDHEA, sAA), and performance outcomes. Therefore, we hope to provide a more comprehensive understanding of individuals’ psychophysiological and behavioural stress responses. To the best of our knowledge, this project is also the first to explore and evaluate challenge and threat parameters in the unique context of BBN encounters. By doing so, we expand the framework to motivated performance situations in the medical field.

### Possible pitfalls

We are aware that the present project is ambitious, which brings several possible challenges.

First, participation in the project will not be part of the regular medical study program but will rather be offered as an extracurricular learning opportunity. Although we assume that medical students have a general interest in communication training, we still rely on voluntary participation.

Second, medical students represent a distinct group of individuals compared to previous SAR-related research. In the third year, medical students already have a solid understanding of the functionality of their stress response, which is a core aspect of SAR interventions. Importantly, a person’s beliefs about stress (i.e., stress mindset) can affect their situation specific stress appraisal [67]. It remains to be seen how the SAR intervention applied in our study will affect the psychophysiology and performance of medical students specifically. We will investigate this issue by assessing participants’ stress mindset before and after the intervention and use it as control variable for primary analyses.

Third, there are more female medical students enrolled in Swiss universities than male students. Gender creates a possible confounder, given the different psychophysiology [87]. To ensure equal allocation to the experimental conditions, participants will therefore be stratified according to gender. Besides, the menstrual cycle of female participants causes monthly fluctuations of steroid hormones, which influence their psychophysiology. To control for these fluctuations, female participants will optimally be tested during the first week after menstruation. This puts restrictions on participation opportunities.

Lastly, while the BBN scenario is the same for all participants, for feasibility reasons, the SP role will be portrayed by different actors. To minimize any influence from SPs playing their role differently, a professional SP instructor of the Institute for Medical Education will provide detailed and identical training to each SP and ensure comparable acting. Further, SP will be considered as control variable in our statistical analyses. At the same time, because the BBN situation is only simulated, ecological validity could be questioned. Yet, due to the nature of the task, it is not feasible to conduct the experiment with real patients. It has been shown that communication skills performances exhibited in settings with SPs can predict performances in real clinical life [105].

## Data Availability

Not applicable.

## List of Abbreviations

BBN: Breaking bad news
BPSM: Biopsychosocial model
CO: Cardiac output
DASS-21: Depression Anxiety and Stress Scale
DHEA: Dehydroepiandrosterone
ERQ: Emotion Regulation Questionnaire
glBAS: Global Breaking Bad News Assessment Scale
HPA: Hypothalamic-pituitary-adrenal
HR: Heart rate
MAP: Mean arterial pressure
MDMQ: Multidimensional Mood State Questionnaire
PEP: Pre-ejection period
sAA: Salivary alpha-amylase
SAM: Sympathetic-adrenal-medullary
SAR: Stress arousal reappraisal
sC: Salivary cortisol
sDHEA: Salivary dehydroepiandrosterone
SMM: Stress Mindset Measure
SP: Simulated patient
SV: Stroke volume
TPR: Total peripheral resistance
WE: Worked example
